### ***Baseline testing***

In the period of 6 to 24 months after the start of the CI rehabilitation the baseline testing and the prolonged stimulation period will be conducted. The full schedule of the baseline testing day can be found in chapter 3, table 3. The CI and VI fitting will be completed for all patients before the first patient starts with the baseline testing and prolonged stimulation (see chapter 3.2 and 10.4). The maximum time period between baseline testing and prolonged stimulation will be kept short (in the order of a few months) to ensure that the results from baseline testing serve as a good control for the prolonged stimulation period.

During the baseline testing day, the control measurements (VI-OFF) will be conducted for all vestibular outcome parameters. This includes the DVA, 3D HIT, fHIT, torsion swing, perception platform and gait and balance tests. The 3D HIT, fHIT and torsion swing tests are performed twice in a row: Once with an active CI and once without. This way the potential influence of CI stimulation on vestibular function and vice versa can also be characterized. Alongside the vestibular tests, an aided CNC hearing test with the regular CI processor will also be conducted.

The patient will also be asked to fill in a set of questionnaires at home and bring them to the hospital during the baseline testing day. At the end of the day the patient will be asked to fill in the VAS-based list of questions.

### ***Prolonged stimulation period***

The prolonged stimulation period consists of 4 days of stimulation per week, for 3 weeks. A full schedule of the prolonged stimulation period is given in chapter 3, table 4. Each stimulation period is scheduled from Monday to Thursday. During this time, the patient will be staying in a hotel next to the hospital (i.e. from Sunday afternoon until Friday morning) and spend their days from approximately 08:30 until 17:30 in the hospital. Friday until Sunday are reserved as a resting period at home.

During the prolonged stimulation period the patients will only use the CVI processor while they are under supervision by a member of the research team in the hospital. This means that patients will make use of the CVI around 8 hours per day, for 4 days in a row. At any other time they will use their own CI processor, only providing CI functionality without vestibular stimulation. The schedule of testing for each week is kept the same. The main parameter that will change between the different weeks is which stimulation algorithm will be used (see figure 6): (A) baseline stimulation with motion modulation (B) reduced baseline stimulation with motion modulation (C) baseline stimulation with no motion modulation. Baseline stimulation consists of constant stimulation of the vestibular nerves at 50% of DR. Reduced baseline stimulation consists of constant stimulation of the vestibular nerves lower than 50% of DR. Motion modulation consists of stimulation of the vestibular nerves based on angular head movement. The parameters (e.g. level of baseline stimulation and modulation) of each paradigm will be determined after analyzing the results of VI fitting. The sequence of stimulation algorithms will be single blind and randomized for each patient. In this way, the patients will serve as their own control.

[figure not shown]

**Figure 6: Stimulation algorithms used during the trial. (A) baseline stimulation with motion modulation (B) reduced/no baseline stimulation with motion modulation (C) baseline stimulation with no motion modulation.**

For all activities during the prolonged stimulation week, ample time is reserved to keep the feasibility of the schedule high and the burden on the patients low. For the same reason a considerable amount of breaks are included in the schedule. During this time the patient can rest and perform leisure activities like reading or walking around within the hospital.

Each day of CVI stimulation will start and end with impedance measurements and a check of UCLs. This is done as a safety precaution to make sure that the implant is performing as expected, even though it is expected that these parameters will not change during the prolonged stimulation period. These measurements will take only 5 minutes to complete. After this, one hour is reserved on Monday and half an hour on every following day to allow the patient to get used to the stimulation. Previous research by the Geneva-Maastricht group has shown that habituation to stimulation at 50% of the DR takes around 30 minutes for the first time the nerves are stimulated, and progressively less time at the start of each consecutive stimulation period. By taking this time every morning for the patient to get used to the stimulation, the reproducibility of the measurements will increase. At the start of every day the patients will also be asked if any (S)AE's occurred after leaving the hospital the previous day (i.e. attacks of nausea or vertigo). At the end of each prolonged stimulation day, the patients will be asked to fill in the VAS based list of questions to characterize their experiences with the CVI on a daily basis.

All the tests which will be conducted during the prolonged stimulation weeks are shown in table 4 of chapter 3 and described in chapter 8.3.1 through 8.3.5. All testing will occur during the four days of prolonged stimulation, except for three perception tests, one performed each Sunday afternoon before every period of prolonged stimulation. The patient will be asked to arrive in the hospital around 16:00 on Sunday for 1 hour of testing. The patient will be tested while using their regular CI processor. The goal of the tests is to assess if any change occurs in the baseline measurement after the patient has performed the perception platform test a few times. This is to exclude any chance that a learning effect might occur for the perception platform test, which is something that has not yet been fully studied. At the end of this test the patient will also be asked to fill in the VAS based preference scales.

Besides testing, the patients will also follow a rehabilitation program for 3 hours every week. During the allocated time-slot every Monday an individual diagnosis for each patient is established and the patient will be asked about their personal goals they would like to achieve in combination with the CVI using the PSFS questionnaire. Based on this a rehabilitation program will be set up and repeated every week in the same fashion. The main focus of the rehabilitation will be placed on achieving the personal goals of each patient and to challenge the patient in using their CVI to the fullest.

At the end of each prolonged stimulation period the patients are asked to fill in a set of questionnaires to gather specific information for the HTA and to evaluate CVI functionality for each stimulation algorithm.

#### ***CI follow-up visits***

For the regular clinical CI rehabilitation care the patient is asked to visit the hospital at regular intervals for a check-up (see chapter 3, table 1). During these visits of around 2 hours another 4 hours are added on average to also perform a VI check-up. This VI check-up will include tests similar to the tests which were performed during the fitting week and/or prolonged stimulation period. During these tests the VI electrodes will be stimulated and response to stimulation will be characterized. The main purpose is to test whether electrode impedances and vestibular responses remain constant over time. Also during these visits additional hearing tests and questionnaires will be administered.

At the 1, 2 and 5 year follow-up visits a CBCT scan will be made to assess if any change occurs on the position of the electrodes inside the SCCs and the cochlea. This information can then be linked to device efficacy and it can be used to assess potential causes of problems with the CVI if they occur. It will also allow for evaluating the benefit from postoperative scanning in the follow-up of the CVI.

#### **8.4. Withdrawal of individual subjects**

Patients can leave the study at any time for any reason if they wish to do so without any consequences. The investigator can decide to withdraw a subject from the study for urgent medical reasons.

As stated in chapter 4.2 and 4.3, patients who make use of VOR suppressing medications will either be asked to stop using this medication before joining the trial (in the case of cinnarizine), or will not be included (in the case of psychiatric medication, e.g. benzodiazepines). However, it can occur that the patient will start taking these medications after they have been included in the trial. If this occurs, it will be noted as a confounder due to the potential effect these medications can have on the VOR response. It will not be seen as a reason for the withdrawal of the patient since the use of these medications does not affect the safety of the patient in the trial and excluding a patient is more detrimental to the usability of the overall data than the potential effect VOR suppressing medications might have. The patients will be notified that they have to inform the research team if they start using VOR suppressing medications (see section E of the standard research file).

Pregnancy is also stated as an exclusion criteria for the trial. However, pregnancy will also not be seen as a reason for the individual withdrawal of a patient. If a patient becomes pregnant, all trial activities which might pose a risk to the pregnancy will be postponed or cancelled until after the pregnancy. Postponing or cancelling will have a smaller influence on the usability of the data gathered in this trial than the

outright withdrawal of a patient. By individually changing the trial schedule there will be no risks for the patient or the pregnancy. The patients will be notified that they have to inform the research team in case of pregnancy (see section E of the standard research file).

Due to the novelty of this study, situations might occur which can cause unforeseen discomfort or side effects for the patient. If this occurs, for example caused by certain stimulation algorithms or measurements, the patient will always have the choice to not undergo a certain part of the trial activities. The planning will then be adapted to this patient specifically to decrease the burden on the patient, and this will not necessarily be seen as a reason for individual patient withdrawal.

A specific patient will be withdrawn from the regular trial activities if, after multiple fitting attempts, it is established that none of the three vestibular electrodes are able to elicit a vestibular response. This patient will however be offered a detailed examination of potential factors which might have caused this result (e.g. etiology, inner ear and nerve anatomy, electrode placement) and a follow-up plan will be made depending on these results. Unrelated to this follow-up plan, the patient will still receive all the regular care associated with receiving a CI.

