## 8.2. Randomization, blinding and treatment allocation

During the implantation, CI fitting, VI fitting and baseline testing the researchers and patients will not be blinded since these procedures will be identical for all patients. However, during the prolonged stimulation period patients will be blinded to which type of stimulation algorithm is used. The three types that will be tested will each be randomly assigned to one of three 4-day prolonged stimulation periods. This way the effect of different stimulation algorithms can be assessed both within patients and between patients.

The sequence of stimulation algorithms will be randomized and single-blinded. Randomization will be performed by using a block randomization-based design. Since there are 3 stimulation algorithms which will be randomized over 3 time periods, each algorithm appearing only once, there are 6 distinct algorithm sequences. To equally distribute all the patients over 6 algorithm sequences a block size of 6 is used. A custom “urn” will be created in the following way: Each of the 6 possible algorithm sequences is added to the urn once. Additional algorithm sequences are chosen at random without replacement from the total of 6 algorithm sequences and also added to the urn. This is done until the amount of algorithm sequences in the urn is equal to the amount of patients which will be included. The urn now contains as many allocation possibilities as there are patients, with each allocation possibility featuring at least once and no more than twice. Randomization will be performed in the period after VI fitting and before the prolonged stimulation period. When an allocation is assigned to a patient during randomization, this allocation is removed from the urn. Therefore, the urn will be empty after all patients have been allocated. This way all possible algorithm sequences will be allocated to at least one patient without offering predictability of algorithm sequence allocation at any moment.

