After obtaining the candidate's written informed consent, a complementary extensive vestibular examination will be done. This VI-inclusion visit will consist of a list of standard vestibular examination tests which are daily, routinely used to investigate the vestibular function in patients with balance disorders. The tests which are included in this list are the caloric test, the oVEMP, the cVEMP, a 3D HIT and a torsion swing test. One extra test, specifically related to the CVI study, will be added: the DVA test. A description of these tests is given in chapter 8.3.1. The complete VI-inclusion visit includes around 3 hours of testing, unless patients were already extensively tested as part of their diagnostic work-up for their pathology. If so, all previously performed tests will be skipped and the VI-inclusion visit will take less time.

Alongside this, a standard CI inclusion procedure will be conducted to assess the patient's eligibility for receiving a CI in the ear to be implanted. This includes hearing tests, an ENT consult and visits to an audiologist, a speech therapist and a social worker. Also an MRI and a neuronavigation CT scan will be made. Any CI eligibility testing that might have been done before as part of regular clinical care will not be repeated.

If the patient meets all inclusion criteria and none of the exclusion criteria as described in chapter 4.2 and 4.3, the patient will be included in the trial. A total of 8 patients will be included. A date will be assigned for the surgical procedure and the patient will be given a set of questionnaires to be filled in at home.

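### Section 8.2 sizes the sequence urn on patients included before surgery but draws from it after fitting withdrawals, so its guarantee that every sequence is used can fail

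*Protocol*

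**What the plan says.** **Urn (Protocol 8.2).** Three algorithms over three weeks mean that "there are 6 distinct algorithm sequences". "Each of the 6 possible algorithm sequences is added to the urn once"; further sequences, all different, are then added "until the amount of algorithm sequences in the urn is equal to the amount of patients which will be included". No sequence may appear more than twice. Drawn entries are removed, and the section concludes that the urn will end empty and that "This way all possible algorithm sequences will be allocated to at least one patient".

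**Timing (8.2).** "Randomization will be performed in the period after VI fitting and before the prolonged stimulation period".

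**Meaning of inclusion (8.3.6, Inclusion).** A candidate who meets the criteria is told that "the patient will be included in the trial", and only then is a surgery date assigned. Section 4.4 uses the word in the same sense when it plans for 8 to 13 patients.

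**Losses in between (8.4, 8.5).** "A specific patient will be withdrawn from the regular trial activities if, after multiple fitting attempts", none of the three vestibular electrodes elicits a vestibular response. Patients may also leave at any time for any reason. Section 8.5 excludes replacement after implantation.

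**Order of work (3.2; 8.3.6, Baseline testing).** Fitting is to be finished in all patients before the first one starts baseline testing and prolonged stimulation.

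**Analysis (10.1).** The algorithms are compared by descriptive statistics only.

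**The concern.** The urn is sized on a count fixed before a planned attrition step and is drawn from after that step. Any loss in between leaves at least one entry undrawn. The statement that the urn ends empty is then false, and whether every sequence is used depends on which entry happens to be left.

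Objective 1c is a primary objective and the only randomised comparison in the trial. Weeks may differ for reasons unrelated to the algorithm: rehabilitation is repeated weekly, adaptation to stimulation is expected, and 8.3.6 itself raises a learning effect for the perception platform. Because 10.1 plans no model that adjusts for week, balance in the allocation is the main protection, and the 8.2 guarantee is meant to support that balance.

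**Working it through.** **Inputs.** Six sequences; N included, from 8 to 13 (4.4); an urn with each sequence once plus N − 6 different sequences a second time (8.2). So N − 6 sequences have two entries and 6 − (N − 6) = 12 − N have one. The number of losses before randomisation, w, is not given in the documents; w = 1 and w = 2 are shown as conditions. Draws are random without replacement, so the undrawn entries are a random subset of the urn.

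**The plan's own claim, w = 0.** Every entry is drawn, so the probability that a sequence is unused is 0 for N = 8 to 12. The guarantee reproduces. N = 13 cannot be filled under the no-more-than-twice rule, since 2 × 6 = 12.

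**One loss.** A sequence is unused only if the one undrawn entry is a single copy: P = (12 − N)/N.

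**Two losses.** No sequence is unused only if both undrawn entries come from doubled sequences and from different ones. There are C(N − 6, 2) pairs of doubled sequences and 2 × 2 = 4 ways to take one copy of each, so P(unused) = 1 − 4·C(N − 6, 2)/C(N, 2).

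| N included | one loss | two losses |
|---|---|---|
| 8 | 4/8 = 50% | 1 − 4/28 = 86% |
| 9 | 3/9 = 33% | 1 − 12/36 = 67% |
| 10 | 2/10 = 20% | 1 − 24/45 = 47% |
| 11 | 1/11 = 9% | 1 − 40/55 = 27% |
| 12 | 0/12 = 0% | 1 − 60/66 = 9% |

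Full enumeration of the urns gives the same values, and a simulation of 200,000 urns at N = 8 with one loss gave 0.499.

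**Effect on week balance, N = 8.** For each possible urn and each set of undrawn entries, count how many patients receive each algorithm in each week (nine cells) and take the largest count minus the smallest.

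- One loss, 7 randomised, as written: the difference is 1 in 50% of outcomes (counts 2 to 3), 2 in 20% (1 to 3) and 3 in 30% (1 to 4). No cell is empty.
- One loss, urn built for 7: the difference is always 1.
- Two losses, 6 randomised, as written: all cells are equal in 14% of outcomes, and some cell is empty in 13%.
- Two losses, urn built for 6: every cell holds exactly 2.

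**After the change.** With the urn sized on the number randomised, no entry is left over at randomisation. The probability of an unused sequence is 0 for 6 to 12 randomised patients. With 5 or fewer, no urn can cover six sequences.

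**The case against.** **Section 8.2 can be read charitably.** It does not say when the urn is filled. It also says that the urn holds as many entries as there are patients, and that it is empty once all are allocated. Since all patients are fitted before stimulation starts, non-responders are known by the time the urn is needed. Read as sized on the patients being allocated, the section is coherent and its guarantee holds. This stands as a reason for low severity. It does not remove the point: 8.2 names the count to use, and the protocol's own use of that word places the count before surgery.

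**The figures are conditional.** No rate is given for total non-response or for other early withdrawal, and 8 is both the planned minimum and the worst row of the table. One loss leaves one entry undrawn, which need not be a whole sequence. All of this stands.

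**A reader might infer that a lost sequence aliases algorithm with week.** The design does not support that. Each algorithm-week cell is covered by two of the six sequences, so losing one sequence empties no cell. At N = 8 with one loss, a model with patient, week and algorithm effects remains estimable in every outcome. Relative to a balanced design, the mean variance inflation of the algorithm contrasts is 1.05 as written and 1.02 after the change. What remains is partial confounding of unadjusted descriptive means.

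**Some imbalance exists anyway.** A full urn of 8 already gives cell counts ranging up to 2 to 4. Losses after randomisation, including patients who decline a particular algorithm under 8.4, can unbalance the sequences whatever the urn. Both are true; the change addresses only the avoidable part.

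**Conclusion.** The point holds as a minor one. On the text as written, any loss between inclusion and randomisation falsifies the statement that the urn ends empty, and it can break the guarantee that every sequence is used, with the conditional probabilities tabulated above. This rests on taking inclusion in the 8.3.6 sense and on the urn not being resized; nothing in 8.2 provides for resizing.

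The consequence is confined to objective 1c, where unadjusted descriptive summaries by algorithm would carry more of any week effect than they need to. A reader might also infer a threat to the efficacy conclusion. There is none: the VI-ON versus VI-OFF Wilcoxon comparison in 10.1 is made within patients and does not depend on sequence balance. The withdrawal rule in 8.4 is only the trigger and is not in question; the sentence to correct is in 8.2.

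**What to change.** In 8.2, replace the count of patients to be included with wording such as: the urn is built after VI fitting has been completed for all patients, and its size equals the number of patients who have not been withdrawn and will enter the prolonged stimulation period. That number is available at that moment because of the order of work set in 3.2 and 8.3.6. It would help to add that the guarantee applies when 6 to 12 patients are randomised.

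The cost is one sentence. No patients, time or data are lost, and no clinical rule changes.

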#### 8.4.1. *Specific criteria for withdrawal (if applicable)*

- Not applicable -

### 8.5. Replacement of individual subjects after withdrawal

Due to the limited number of implantable devices available, patients will not be replaced if withdrawal occurs after implantation. However, the possibility of a drop-out has been accounted for in the sample size calculation.

### 8.6. Follow-up of subjects withdrawn from treatment

Subjects who withdraw from the trial after implantation will still receive regular CI care, including the rehabilitation and check-up visits which are part of standard clinical practice. During these visits, the state of the implant is monitored as is normal with a regular CI implant. Any (S)AE's which might have occurred will be logged.

### 8.7. Premature termination of the study

The study will be halted or terminated prematurely if any of the below-mentioned situations occur:

- if the judgement of the competent medical research ethics committee that has assessed the study is irrevocably revoked;
- if a reasonable case can be made for terminating the study in the interests of the health of the research subjects;
- if it transpires that continuation of the study cannot serve any scientific purpose, and this is confirmed by the medical research ethics committee that has issued a positive decision on the study;

- if one of the parties or the funder has been declared insolvent or a bankruptcy/winding-up petition has been filed in respect of one of the parties or the financier, or one of the parties or the financier is dissolved as a legal entity;
- if the principal investigator is no longer capable of performing the tasks of the principal investigator, and no replacement agreeable to both parties can be found;
- if one of the two parties fails to comply with the obligations arising from the agreement and, provided compliance is not permanently impossible, this compliance has not taken place within thirty days of the defaulting party receiving a written request to comply, unless failure to comply is not in reasonable proportion to the premature termination of the study;
- if circumstances beyond the control of the sponsor, investigator or funder make it unreasonable to require the study's continuation.

